## Study Objectives and Endpoints

### Primary Objective

The primary objective of this study is to evaluate if intrathecal pump refills at home are better for patient comfort compared to intrathecal pump refills at the hospital. The primary outcome measure, i.e. patient comfort, is evaluated with the General Comfort Questionnaire (GCQ).

### Secondary Objectives

The secondary objective is to evaluate if there is a difference in health-related quality of life, pain intensity, pain interference, stress, anxiety, general self-efficacy, burden among caregivers, patient preference for the location of the refill and in number of (serious) adverse events (e.g., infection, overdose). The third objective is to conduct an economic evaluation of intrathecal pump refills at home versus at the hospital, based on healthcare expenditure and (in)direct costs.

### Endpoints

During the baseline assessment, patients are asked to provide information on their demographic and socio-economic background—including sex, age, marital status, ethnicity, years of education, highest

obtained degree, employment status, income, whether or not they receive home care or have an informal caregiver, and household composition — as well as clinical baseline data, such as the year of pump implantation, medication, indication for having an IDD pump. The general data protection regulation principle of data minimization and proportionality will always be considered.

Further, patients will receive questionnaires related to our primary and secondary outcome measures, as described below. Following this initial assessment, patients will be randomized. The randomization list will be created in R, whereby each patient will receive two refills in the outpatient clinic and two refills at home in a randomized order. After each refill, all baseline outcome measures will be reassessed. In addition, secondary outcomes such as patient satisfaction and preference, telemonitoring quality (applicable only for home refills), and safety will be evaluated during follow-up assessments. Health expenditure data will be collected through phone calls. The researchers will call each patient four weeks after the first refill and four weeks after the second refill. Questions will be asked concerning health-economic aspects. These questions will be based on the following variables: consultations, adverse events, hospitalizations, medication, other health-related costs. For more details concerning these questions, we refer to the health economic telephone interview. To prevent test order effects, the test order of the self-reported measures will be randomized for each individual patient at each assessment. After the fourth refill patients will be asked to complete a Discrete Choice Experiment (DCE). Table 1 (section 15) provides an overview of the outcomes, the timing of assessments, and the designated respondents for each questionnaire.

The self-reported measures will be completed online via REDCap (Research Electronic Data Capture) to enhance study feasibility and ensure data security. For participants who are unable to complete the questionnaires online, or in cases where internet connectivity is limited, paper-based versions of the questionnaires will be available.

#### Primary outcome

The primary outcome of this study is patient comfort, selected specifically to determine whether HAH care provides benefits for patients with chronic non-cancer pain and spasticity. This concept is grounded in Kolcaba's mid-range theory of comfort, which defines comfort as "The immediate experience of being strengthened by having needs for relief, ease, and transcendence met in four contexts: physical, psychospiritual, sociocultural, and environmental, and it is so much more than the absence of pain" (50,51). Patient comfort is evaluated with the General Comfort Questionnaire (GCQ), a self-reported instrument consisting of 48 items that reflect the physical, spiritual, environmental and social dimension (50). Responses are rated on a four-point Likert scale ranging from "strongly disagree" to "strongly agree". Some items are reverse scored during data processing, with higher overall scores indicating greater levels of comfort (52).

#### Secondary outcomes

##### Quality of life (QoL)

The McGill Quality of Life Questionnaire (MQOL) consists of 17 questions. 16 of these are rated on an 11-point Likert scale (range from 0 to 10) and assess various domains including physical symptoms, physical wellbeing, psychological symptoms, perception towards life and sense of achievement (53,54). The final part is an open question. Higher scores reflect a better QoL (53). Originally this questionnaire was developed for palliative patients (54), the MQOL has since been validated for patients with chronic conditions (53). It captures a multidimensional view of QoL by evaluating physical wellbeing, psychological wellbeing, existential wellbeing, social support, and physical symptoms, along with an overall QoL rating (53).

Additionally, the EuroQol with five dimensions and five levels (EQ-5D-5L) will be assessed. Based on the Belgian EQ-5D-5L value set developed by Bouckaert et al. (2022), index scores range from -0.42 to 1 (with 0 corresponding to death and 1 to full health), as derived from population preferences (55).

### Pain intensity

The Visual Analogue Scale (VAS - 100 mm) in electronic format will be used for the assessment of current pain intensity. The VAS pain score is reliable, valid, and sensitive to change (56,57). VAS measurements are found to have good test-retest reliability (58).

### Pain interference

Pain interference refers to the degree to which pain hinders or restricts an individual's physical, emotional, and social functioning (59). The Patient-Reported Outcomes Measurement Information System (PROMIS®) was developed to provide a standardized, valid, and reliable measure of clinical outcomes across diverse patient populations (60). The NIH-funded PROMIS Pain Interference measure assesses the impact of pain on key aspects of an individual's life. It evaluates the extent to which pain disrupts engagement in social, cognitive, emotional, physical, and recreational activities. The PROMIS Pain Interference item bank has demonstrated strong psychometric properties, including reliability and construct validity, supporting its use as an outcome measure in chronic pain settings (59).

### Stress

Exposure to acute psychological stress triggers two primary physiological systems: the sympatho-adrenal medullary (SAM) system and the hypothalamo-pituitary-adrenal (HPA) axis (61). Activation of the SAM system leads to the rapid release of catecholamines—adrenaline and noradrenaline—which stimulate increases in heart rate and blood pressure (62). This response is also marked by elevated levels of salivary alpha-amylase, a biomarker of sympathetic nervous system activity (61,63). The HPA axis contributes to the longer-term stress response through the release of cortisol from the adrenal glands (61,62,64). Saliva samples will be collected to measure cortisol levels. This provides a non-invasive and valuable method for assessing HPA-axis activity and stress levels (65). These samples will be obtained with synthetic salivettes (Sarstedt AG & Co., Nümbrecht, Germany) 5 min before the start of the refill procedure, immediately after the refill procedure and 10 minutes afterwards. Saliva samples will be stored at -20°C until analysis. The saliva samples will be analysed using the Cobas 8000: Elecsys® Cortisol II, electrochemiluminescence immunoassay.

### Patient anxiety

Patient anxiety will be provided through the State Trait Anxiety Inventory (STAI). The STAI, developed by Spielberger, Gorsuch, and Lushene, is designed to provide an objective assessment of anxiety levels in psychologically healthy adults (66). This questionnaire consists of 40 Likert-type items on a four-point scale. STAI is widely used in chronic pain research to assess anxiety, as it captures both acute anxiety symptoms and anxiety as a stable trait of the patient's personality (66,67). For both types of anxiety, the total score ranges from 20 to 80, with higher scores indicating higher levels of anxiety. The STAI is a highly reliable measure that can discriminate between high- and low-stress situations (66).

### Self-efficacy

The General Self-Efficacy (GSE) Scale is a 10-item self-report questionnaire used to assess perceived self-efficacy. This construct reflects an individual's belief in their ability to cope with challenging situations and to successfully achieve goals (68,69). In the context of chronic pain, it encompasses not only the expectation of being able to perform specific tasks or behaviors, but also the confidence to do so despite the presence of pain (69–71). Higher self-efficacy scores have shown to be associated with lower pain intensity levels, better physical health-related QoL, better mental health related QoL, lower catastrophizing, and use of coping strategies (70,71). The GSE Scale has been used in chronic pain conditions (72). Its validity was assessed in participants dealing with stressful health-related situations (73).

### Caregiver burden

To evaluate caregiver burden, the Zarit Burden Interview (ZBI) questionnaire will be completed (74). This 12-item self-report instrument assesses caregiver burden and is a shortened version of the original 22-item Zarit Burden Scale (75–77). Each item is rated on a 5-point scale, with higher scores indicating greater burden; a score of 4 on any item reflects the highest level of perceived strain. The total score ranges from 0 to 48, with higher totals reflecting more significant caregiver burden. The questionnaire focuses on aspects such as time demands, physical health, mental strain, and psychosocial stressors (75).

### Patient satisfaction

Patient satisfaction is evaluated with a seven-point Likert scale asking the patient to rate the overall level of satisfaction with the refill at home.

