| Assessment                       | 
Saliva samples will be obtained with synthetic salivettes (Sarstedt AG & Co., Nümbrecht, Germany) at three different time points: five minutes before the refill, just after the refill and ten minutes after the refill.
 
Immediately after the termination of the teleconnection, the patient will receive a tablet with a link to the relevant questionnaires in the data collection tool. The test order will be randomized, but all will include: GCQ, MQOL, EQ-5D-5L, VAS, PROMIS, STAI, Likert-scale for patient satisfaction, GSE and questions about safety. Additionally, caregiver burden will be assessed using the ZBI. The quality of telemonitoring, duration of the consultation, and safety will be monitored by the researchers (at home and at the hospital).
 
All the above-mentioned data is study-specific, assessment does not occur during routine practice.
                                                                                                                                                                                                                                                                                                                                                                                                                                                   |

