|-----------------------------|----------------------------------------------------------------------------------------------------------------------------------------------------------------------------------------------------------------------------------------------------------------------------------------------------------------------------------------------------------------------------------------------------------------------------------------------------------------------------------------------------------------------------------------------------------------------------------------------------------------------------------------------------------------------|
| Description          | 
The control intervention consists of standard care. Five minutes before the refill, a saliva sample will be obtained. These synthetic salivettes will be provided by the researchers in each participating center.
 
The refill procedure will be carried out by the physician, following the standard care protocols currently in place at each participating hospital. During the visit, the pump settings are first read out, after which the sterile refill procedure is performed. The intrathecal pump is then refilled with the medication prescribed for the individual patient, either morphine, baclofen, adjuvantia or a combination of them.
 |
| Assessment           | 
After the consultation, the patients will receive a tablet with the relevant questionnaires in the data collection tool. The test order will be randomized, but all will include: GCQ, MQOL, EQ-5D-5L, VAS, PROMIS, STAI, GSE, Likert-scale for patient satisfaction and questions about safety. Additionally, caregiver burden will be assessed using the ZBI. The duration of the consultation, and safety will be monitored by both the researcher at home and the one at the hospital.
 
All the above-mentioned data is study-specific; assessment does not occur during routine practice.
                                                          |

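### The protocol contradicts itself on hospital-visit data for two secondary outcomes: satisfaction is defined for the home refill only, and the hospital procedure lists one saliva sample where the outcome definition requires three

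*Protocol*

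**What the plan says.** **Satisfaction.** Section 6.3.2 (Patient satisfaction) gives the only definition: a seven-point Likert scale "asking the patient to rate the overall level of satisfaction with the refill at home". The hospital visit in section 9.2 (Control intervention, Assessment) nevertheless includes it among the questionnaires: "GCQ, MQOL, EQ-5D-5L, VAS, PROMIS, STAI, GSE, Likert-scale for patient satisfaction and questions about safety". The home visit has it as well: "STAI, Likert-scale for patient satisfaction, GSE and questions about safety". In section 6.3 the restriction to home refills is attached to telemonitoring alone: "patient satisfaction and preference, telemonitoring quality (applicable only for home refills), and safety will be evaluated during follow-up assessments". Table 1 agrees: satisfaction is scheduled after each refill, and the home-only marker sits on the telemonitoring column. The protocol summary (section 4, Endpoints) names satisfaction among the outcomes on which the two arms are compared.

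**Stress.** Section 6.3.2 (Stress) sets the saliva samples at "5 min before the start of the refill procedure, immediately after the refill procedure and 10 minutes afterwards", with no limit by location. The home procedure in section 9.2 repeats the three times. The hospital procedure (Control intervention, Description) says "Five minutes before the refill, a saliva sample will be obtained" and does not mention the other two. Stress is also named as a between-arm outcome in the summary.

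**Who records at hospital visits.** For the hospital visit, section 9.2 says that duration and "safety will be monitored by both the researcher at home and the one at the hospital". Section 9.2 (Intervention team) describes the researcher at home as the person who travels to the patient and carries out the home refill. The hospital refill is done by the physician.

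**Baseline stress.** Table 1 marks stress as a baseline measure, section 10.4.1 reports it at baseline, and section 10.4.2 names it as a potential confounder. Section 6.3.2 times the saliva samples only relative to a refill.

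**The concern.** These passages tell staff what to ask and what to collect, so they are not details that a statistical analysis plan would settle. A comparison between settings needs the same question and the same sampling times in both.

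A patient who has just been refilled in hospital and is asked to rate the home refill is rating a different event. If the first study refill is in hospital, there is no study home refill to rate yet.

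Hospital refills follow each participating hospital's own standard care, so section 9.2 is where a centre will look for what the study adds. A centre working from that section alone would take one saliva sample and stop. A sample not taken around a procedure cannot be recovered afterwards, and no analysis can replace a setting in which the post-refill measurement was never made.

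**Working it through.** The protocol states no total number of samples or ratings, so there is no figure to reproduce. The check sets the passages side by side and then counts what is exposed.

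**Side by side**

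| Item | Outcome definition (6.3.2) | Home visit (9.2) | Hospital visit (9.2) | Table 1 |
|---|---|---|---|---|
| Satisfaction | Home refill only | Scale given | Scale given | After each refill, no home-only marker |
| Saliva samples per refill | 3, any location | 3 | 1 (pre-refill) | Baseline and after each refill, no home-only marker |

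For satisfaction, the definition is the outlier: section 9.2, section 6.3, Table 1 and the summary all apply the scale in both settings. For saliva, the hospital procedure is the outlier.

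**Inputs.** 82 patients, with two hospital and two home refills each (section 7.1). Samples per refill are as in the table. Counts are for 82 patients before dropout.

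**Satisfaction ratings after hospital refills**

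82 x 2 = 164

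**Refill saliva samples if section 6.3.2 governs both settings**

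- Home: 82 x 2 x 3 = 492
- Hospital: 82 x 2 x 3 = 492, of which 82 x 2 x 2 = 328 are post-refill
- Total: 984, or 12 per patient

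**Refill saliva samples if section 9.2 is followed literally**

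- Home: 82 x 2 x 3 = 492
- Hospital: 82 x 2 x 1 = 164, none post-refill
- Total: 656, or 8 per patient

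The difference is 984 - 656 = 328 samples, all from hospital refills and all post-refill.

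**Allowing for dropout.** Section 11.3 allows for 20% loss to follow-up. If all of that loss occurred before the first refill, the counts would be 0.8 x 164 = 131 ratings and 0.8 x 328 = 262 samples.

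**Order of refills.** Section 7.2 pairs one home and one hospital refill and randomizes the order, which gives 2 x 2 = 4 tracks. Two of the four begin in hospital. On those tracks the first satisfaction rating comes before any study home refill.

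**Baseline stress.** Randomization takes place in the week after the baseline visit (section 7.2), so the baseline assessment precedes the first study refill. With sampling defined only around a refill, no sample that could supply the baseline value is defined.

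**The case against.** The strongest reply is that this is loose drafting and the governing text is clear. Section 6.3.2 is the outcome definition, it sets three samples around the refill without limit of place, and Table 1 puts its home-only marker on telemonitoring alone. The hospital procedure does not say that only one sample is taken; it mentions one and is silent on the rest. The satisfaction sentence may be a paraphrase: the questionnaire itself is not shown, and asking patients about a home refill they have not yet had is an implausible intention. Much of this stands. It is why the point is a contradiction to reconcile and not proof that data will be lost.

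A reader might infer more: that both home-versus-hospital comparisons lack valid control data, or that neither outcome can be compared. The documents do not support that. Satisfaction is scheduled and given at hospital visits; the defect is in how the item is described. For cortisol, the pre-refill sample is listed in both settings, so that comparison survives even the most literal reading.

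A reader might also add that home and hospital samples are not tied to the same time of day. The protocol states nothing wrong there. The only support would be the title of a cited reference on diurnal patterns, so it is no part of this point.

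On who records duration and safety, the two researcher titles may simply be names for team members, and section 6.3.2 (Safety) does assign safety ratings to both. No loss of data is shown. What remains is that the hospital text gives a task to someone for whom no role at hospital visits is described.

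The objection does not remove the operational risk. Hospital refills take place at each participating hospital, and section 9.2 describes what is done there.

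**Conclusion.** The point holds as an internal contradiction in data-collection instructions for two secondary outcomes that the protocol compares between arms. If sections 6.3.2 (Patient satisfaction) and 9.2 (Control intervention) are followed as written, up to 164 hospital satisfaction ratings would concern the wrong event and up to 328 post-refill hospital saliva samples would not be taken. The change in cortisol around the procedure would then have no control data; the pre-refill comparison would remain.

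These are upper counts. They assume 82 patients without dropout, every centre reading the text literally, and a satisfaction item worded as section 6.3.2 describes it. If centres work from the general saliva definition and the actual item is neutral, nothing is lost.

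The primary comfort comparison and the sample size are unaffected. The text should be corrected all the same, because samples not taken cannot be collected later and the correction is cheap. The undefined baseline stress sample is a separate but related gap, since that value is planned for reporting and possible adjustment.

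**What to change.** 1. Section 6.3.2 (Patient satisfaction): word the item for both locations, asking about satisfaction with the refill just received. Check that the questionnaire in REDCap and its paper version say the same.
2. Section 9.2 (Control intervention): state all three saliva times for hospital refills, so that the text agrees with section 6.3.2 (Stress) and with the home procedure.
3. Section 9.2 (Control intervention, Assessment): state who records duration and safety at hospital visits.
4. Baseline stress: either define when and how the baseline saliva sample is taken, or remove baseline stress from Table 1 and from sections 10.4.1 and 10.4.2, with the matching text in the summary and section 6.3.

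The cost is a few sentences in an amendment and a check of the questionnaire wording. The hospital samples are already planned under section 6.3.2, so item 2 adds no new measurement. Only item 4 could add one, if a baseline sample is kept. The changes are most useful before further hospital refills take place.

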### Tele-monitoring quality

The quality of tele-monitoring will only be evaluated after a home-filling by the researcher at home and the researcher in the hospital. This will be examined using three different Likert scales to score 1) quality of audio, 2) quality of video, and 3) overall quality of the teleconsultation (78).

### Time of the refill

The time required for the procedure will be recorded from two perspectives. First, the time for the refiller will be measured: for home-based refills, this includes the duration from entering the patient's house until departure. For hospital-based refills, it covers the time spent in the patient's room in the outpatient clinic. Second, the time required for medical supervision will be recorded: for home-based refills, this includes the full duration of the online consultation. For hospital-based refills, it includes the time the physician spends in the outpatient clinic with the patient.

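### The two refiller-time clocks are not equivalent: the home clock takes in study-only work by the refiller that the hospital clock need not contain

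*Protocol*

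**What the plan says.** Section 6.3.2 (Time of the refill) sets out two perspectives on duration.

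- Refiller time, home: "for home-based refills, this includes the duration from entering the patient's house until departure".
- Refiller time, hospital: "For hospital-based refills, it covers the time spent in the patient's room in the outpatient clinic".
- Supervision time, home: "for home-based refills, this includes the full duration of the online consultation". In hospital it is the physician's time with the patient in the clinic.

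Section 9.2 says who does what. At home, one visiting researcher performs the refill while a second follows remotely. Saliva is taken "five minutes before the refill, just after the refill and ten minutes after the refill". The questionnaires follow: "Immediately after the termination of the teleconnection, the patient will receive a tablet with a link to the relevant questionnaires". On the status of these assessments the section states: "All the above-mentioned data is study-specific, assessment does not occur during routine practice".

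For the control arm, section 9.2 has the physician perform the refill and the researchers supply the salivettes. The questionnaires come later: "After the consultation, the patients will receive a tablet with the relevant questionnaires in the data collection tool". Section 6.3.2 (Stress) gives the same three saliva times without limiting them to home refills: "5 min before the start of the refill procedure, immediately after the refill procedure and 10 minutes afterwards".

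The Protocol Summary lists consultation time among the secondary outcomes on which the arms are compared.

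**The concern.** The time measure is introduced as the time the procedure requires. At home, however, the rule measures the whole visit, and the visitor is both refiller and data collector. Nothing in the rule removes the trial's own data collection from the home interval. In hospital the person timed is the physician, who is not described as having to stay for the last saliva sample or the tablet.

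The measured difference would then mix two quantities: the difference in refill time and the difference in research time. Only the first would carry over to routine home care. Because the excess arises at both home refills of every patient, neither the crossover nor a larger sample averages it out. If only entry and departure are recorded, no later analysis can separate the two parts.

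**Working it through.** The Protocol states no expected refill duration, so there is no planned figure to reproduce. The check compares the tasks inside each clock and then bounds the part that the stated schedule fixes.

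**Step 1: what lies inside the refiller clock**

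| Task | Home refiller (visiting researcher) | Hospital refiller (physician) |
|---|---|---|
| Pump read-out and sterile refill | Inside | Inside |
| Telemonitoring set-up | Inside; part of the home intervention | Not described |
| Post-refill ultrasound | Inside; part of the home intervention | Not described in the control procedure |
| Saliva 5 minutes before | Inside; may overlap with set-up | Depends on when the room clock starts |
| Saliva 10 minutes after | Inside; no other staff member is described at the house | Not required to be inside |
| Tablet handover | Inside; follows the end of the teleconnection | Comes after the consultation |
| Completing the questionnaires | Inside only if the researcher stays | Need not be inside |

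**Step 2: effect on the comparison**

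Let T be refill time and w the study-only minutes that fall inside the clock. Then

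measured difference = (T_home − T_hospital) + (w_home − w_hospital).

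The second bracket is the bias. At home the rule puts the study tasks inside the clock. In hospital, w_hospital can be 0. It can also be positive, because the room interval has no start or stop event and saliva is sampled there too.

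**Step 3: the part fixed by the schedule**

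Let u be the minutes after the refill filled by work that belongs to the home refill itself (ultrasound, packing up). The study-only wait for the last sample is

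w = max(0, 10 − u).

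The documents give no value for u, so the range is shown:

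- u = 0: w = 10 minutes
- u = 5: w = 5 minutes
- u = 10 or more: w = 0 minutes

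The tablet handover adds an unstated but presumably short time. The 5-minute pre-refill wait is not counted, because set-up, pump read-out and label checks can fill it.

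**Step 4: the supervision clock**

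At home this clock stops with the teleconnection, which closes once the ultrasound check is satisfactory. The tablet is given only after that, so the questionnaires lie outside it. Saliva sampling before and just after the refill may still fall within it.

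**The case against.** Five points can be made against the concern.

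1. The Protocol Summary speaks of consultation time, and within the time section only the supervision perspective uses that word. If that is the compared outcome, the questionnaires are outside it. This stands as a limit: the concern is confined to refiller time. Refiller time is still defined as an outcome perspective in its own right, and the Protocol does not say which of the two is meant.
2. It is not stated that the researcher stays while the questionnaires are completed. This also stands. The last saliva sample and the tablet handover do not depend on it.
3. Hospital study time is not shown to be zero. Samples are taken there too, and who collects them is not stated. This stands, and it is a second weakness of the definition: without start and stop events, sites could differ in what they include.
4. The home clock starts at the door and leaves out travel, which works in the opposite direction for staff burden. Costs come from claims data, telephone interviews and national tariffs (sections 6.3.2 and 10.4.3). So nothing follows here about total staff time or the ICER.
5. A common end event set at a post-refill check would not suit both arms, because the control procedure describes no such check. This stands, and the fix avoids that event.

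None of these makes the two refiller clocks equivalent.

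**Conclusion.** The concern holds for refiller time. The home and hospital clocks have different boundaries, the home one contains study-only work by the refiller, and the hospital one need not. The likely direction is against home. The size supported by the documents is up to about 10 minutes per home refill, less overlap with the ultrasound check and packing up. The full 10 minutes assumes no overlap and no corresponding wait inside the hospital room clock.

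A reader might infer a larger inflation from the questionnaires. The countable patient items are GCQ 48, MQOL 17, EQ-5D 5, VAS 1, STAI 40, GSE 10, satisfaction 1 and safety 1, so 48 + 17 + 5 + 1 + 40 + 10 + 1 + 1 = 123, plus PROMIS of unstated length. At an assumed 5 to 10 seconds per item this gives 123 × 5 / 60 = 10.25 to 123 × 10 / 60 = 20.5 minutes. The documents do not support this as an expected inflation: they give no time per item and do not say that the researcher waits. Nor do they support a claim that the hospital figure contains no study time.

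A secondary outcome is affected. The primary comfort endpoint is not.

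**What to change.** Amend section 6.3.2 (Time of the refill) as follows.

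- Define refiller time in both settings by events that occur in both, for example from the start of pump read-out to the end of the refill procedure.
- Record the home-only steps (telemonitoring set-up, post-refill ultrasound) as a separate component of the home intervention, so that they are reported and not lost.
- Record the minutes spent on saliva sampling and on questionnaires separately in both settings.
- Compare times net of those study-only minutes, and state whether consultation time in the Protocol Summary means refiller time, supervision time or both.

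The cost is a few extra timestamps in the CRF and a short protocol change. It needs no extra visits or staff and does not alter the refill procedure. It has to be in place at data collection, because entry and departure times alone cannot be split afterwards.
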